#### 3.5.3. Follow-Up Phase (from Intervention Visit to 1 Month)

The follow-up of the enrolled subjects will commence from the intervention visit and will extend to 30 days at the common study termination date.

At 24 h, patients will visit the investigation site for a clinical evaluation, including a physical examination, ECG and echocardiography, the removal of the 24 h ECG halter device and an adverse events assessment. 

At 30 days, a phone-driven follow-up evaluation is conducted for the assessment of any of the study’s outcomes and adverse events (AE). Patients will also be instructed to report earlier to the study center if they have symptoms suggestive of an AE. 

### 3.6. Interventions

Individuals randomized to the flecainide arm will intravenously receive flecainide at a dose of 2.0 mg/kg (maximum dose of 150 mg) throughout the 10 min in the emergency department. Flecainide will be dissolved in a 100 mL D/W 5% solution.

Patients randomized to the amiodarone arm will intravenously receive amiodarone at a dose of 5.0–7.0 mg/kg over 1 h in the emergency department, as well as a follow-up dose of 50 mg/h (a maximum dose of 1000 mg) for up to 24 h (Figure 2). 

Intravenous metoprolol is administered in patients with atrial fibrillation exhibiting a ventricular rate over 100 bpm, according to a physician’s decision. 

Hemodynamically stable patients with an unsuccessful pharmacological cardioversion at 24 h will undergo electrical cardioversion, according to the clinical judgement of the treating physician.

Any prior use of an antiarrhythmic agent will be documented in the case report form (CRF) and all concomitant medications or other therapies will also be documented. For patients withdrawing from the study, the reasons and any follow-on therapy are to be documented in the CRF.

### 3.7. Outcomes

The study’s primary endpoints are the frequencies of successful cardioversion within 6 h of drug administration as well as the combined frequency of PVCs, NSVT, SVT, bradycardia and hypotension during the same time frame. The main secondary endpoints are the frequency of patient discharges from the Emergency Department with a sinus rhythm and the frequency of successful cardioversion to a sinus rhythm within 24 h. All adverse effects, including extracardiac, will be assessed and categorized based on their severity, type and frequency. Table 3 lists all the study primary and secondary endpoints.

### 3.8. Statistical Analysis

All safety and efficacy results will be summarized using descriptive statistics.

The continuous variables will be expressed as mean ± standard deviation or median and interquartile range ((IQR), 25th, 75th percentile) depending on the normality of the distribution. The categorical values will be presented as frequencies and percentages. 

All primary and secondary endpoints will be analyzed according to the “intention to treat” principle, i.e., according to the treatment given, without reference to the treatment compliance or changes. Additional per-protocol sensitivity analyses will be performed.

No statistical adjustment will be performed for multiple secondary endpoints in their analysis, but reporting of all the secondary endpoint analyses will make it clear whether the primary endpoint was statistically significant and will report the number of secondary endpoints proposed as a priori in the study protocol.

A safety assessment will be based on the adverse event reports collected between the signing of the informed consent form and the completion of the final follow-up visit for each participant.

In case of an interim analysis, the Pocock method will be used and a *p*-value of 0.03 for the interim and 0.03 for the final analysis will be used. The data will be analyzed according to the “intention to treat” principle.

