### 3.3. Randomization

Randomization is performed via an eCRF platform developed by PHARMASSIST CRO (Athens, Greece), which is also used to document all the study contacts, assessments and outcomes. 

Patients and researchers are aware of the treatment group that patients have been randomized to. The two antiarrhythmic drugs, amiodarone and flecainide, have different dosages and a different time and method of administration, making the design of a single or double-blinded trial design difficult in an Emergency Department setting. 

The process of active randomization in each of the two groups in a 1:1 ratio contributes to the prevention of selection bias and is undertaken by an independent authorized researcher who is not taking part in the rest of the trial’s procedures.

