#### 3.5.2. Intervention Visit (V0)

The intervention visit is defined as the time at which the study staff intravenously administers the assigned drug and coincides with the screening visit. The drug that will be administered to each patient will be determined randomly, through a simple randomization process, as detailed in the relevant section. Patients in both groups will remain at the ED for a total of 6 h after starting the treatment, regardless of cardioversion status. If no adverse events occur during this time, including an AV block, sinus bradycardia < 50 bpm, syncope, presyncope, or systolic blood pressure < 90 mmHg and a cardioversion to sinus rhythm is successful, the patient will be discharged. Otherwise, the patient will be admitted to the hospital. Patients receiving flecainide with an unsuccessful cardioversion at 6 h will be hospitalized and receive amiodarone. Patients with an unsuccessful drug cardioversion after 24 h will undergo electrical cardioversion, according to the clinical judgment of the attending physician. All patients (i.e., those who were discharged at 6 h following a successful cardioversion and those who were hospitalized) will be under continuous 24 h ECG halter monitoring. The hospitalized patients will also be under continuous ECG monitoring until the time of a cardioversion. The 24 h ECG halter will be removed at 24 h from drug administration initiation, regardless of the cardioversion status.

In case of hemodynamic instability during or after the administration of the drug, or if the Δ (troponin at 1 h) is above the limit of the hospital’s laboratory troponin cut-off levels, the administration of the drug will cease, and the patient will be treated according to the guidelines. At discharge, the administration or non-administration of other medication will follow the guidelines, with the exception that patients will not receive treatment with a class Ic antiarrhythmic agent. 

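### Section 3.8 defines intention to treat as analysis by the treatment given, which contradicts the principle it names and the rest of its own sentence

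*Protocol article*

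**What the plan says.** The rule for grouping patients stands in the protocol article, Section 3.8. It places every primary and secondary endpoint under intention to treat and defines the term in the same sentence: "i.e., according to the treatment given, without reference to the treatment compliance or changes". The next sentence adds a second analysis: "Additional per-protocol sensitivity analyses will be performed". The section closes, after the interim-analysis provision, with "The data will be analyzed according to the “intention to treat” principle", this time without a definition.

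Three other places bear on the point:

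- Section 3.3 on the purpose of allocation: "The process of active randomization in each of the two groups in a 1:1 ratio contributes to the prevention of selection bias".
- Section 3.3 on blinding: "Patients and researchers are aware of the treatment group that patients have been randomized to".
- Section 3.5.2 on later treatment: "Patients receiving flecainide with an unsuccessful cardioversion" at 6 h are admitted and given amiodarone.

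No section states that patients are analysed in the arm to which they were randomised.

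**The concern.** The explanatory clause is the only definition of the analysis groups in the article, and it governs every primary and secondary endpoint. It names one principle and describes another. Intention to treat keeps each patient in the allocated arm, and this carries the protection of randomisation, on which Section 3.3 relies, through to the result. Grouping by treatment given forms the arms after allocation, when the treating team already knows the assignment.

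Departures from allocation are possible here. The trial is open label, and the article's own Discussion describes class IC agents as contraindicated for cardioversion in patients with revascularised coronary disease, a group the trial enrols. If a physician gave amiodarone to a patient allocated to flecainide because that patient looked high-risk, the literal rule would move the patient and any event into the amiodarone arm. A patient who was randomised but received neither drug could not be placed at all. Both co-primary claims, superiority on cardioversion and non-inferiority on safety, rest on the same sentence.

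**Working it through.** **1. The text side by side.** The definition in Section 3.8 has two halves.

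| Part of the definition | What it implies for grouping |
|---|---|
| By the treatment given | Group by the drug actually received |
| Compliance and changes disregarded | Do not regroup for departures from plan |

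The second half is ordinary intention-to-treat language and the first is not. The closing statement of intention to treat adds no definition. The per-protocol analyses cannot settle the matter, because they too depend on what was received. The sentence therefore contradicts itself, and two analysts could build different analysis sets from it.

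**2. Which endpoints are exposed.** Both primary endpoints run from drug initiation for 6 h (Section 3.7, Table 3). The planned amiodarone for flecainide failures starts only after a failed attempt at 6 h (Section 3.5.2), when that window has closed. The 6 h endpoints are exposed only if the first drug given differs from allocation, or if no drug is given.

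**3. The plan's own figure.** The point concerns no stated figure, but the sample size was checked to see whether the fix disturbs it. Inputs from Section 3.4: 65% and 45%, type I error 0.05 (taken as two-sided), power 80%. With pooled variance under the null:

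n = [1.96 × √(2 × 0.55 × 0.45) + 0.842 × √(0.65 × 0.35 + 0.45 × 0.55)]² / 0.20² = (1.379 + 0.580)² / 0.04 ≈ 96 per arm.

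The stated 96 is reproduced. The grouping rule does not enter it.

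**4. Illustration of size.** Inputs: 100 per arm, 65% and 23% conversion (Section 3.4; these are pooled 4 h rates, used here as stand-ins for 6 h). Assumption: s flecainide-assigned patients receive amiodarone at the start. The documents give no value for s, so 0 to 10 is shown, under three assumptions about who switches.

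- **A**, switchers would convert on neither drug. As randomised: 65/100 − 23/100. By treatment given: 65/(100 − s) − 23/(100 + s).
- **B**, switching is unrelated to prognosis. As randomised: [(100 − s) × 0.65 + s × 0.23]/100 − 0.23. By treatment given: 0.65 − 0.23.
- **C**, switchers would convert on either drug. As randomised: 65/100 − 23/100. By treatment given: (65 − s)/(100 − s) − (23 + s)/(100 + s).

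Differences in percentage points, as randomised / by treatment given:

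| s | A | B | C |
|---|---|---|---|
| 0 | 42.0 / 42.0 | 42.0 / 42.0 | 42.0 / 42.0 |
| 2 | 42.0 / 43.8 | 41.2 / 42.0 | 42.0 / 39.8 |
| 5 | 42.0 / 46.5 | 39.9 / 42.0 | 42.0 / 36.5 |
| 10 | 42.0 / 51.3 | 37.8 / 42.0 | 42.0 / 31.1 |

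For s = 5 in A: 65/95 = 68.4%, 23/105 = 21.9%, difference 46.5. In C: 60/95 = 63.2%, 28/105 = 26.7%, difference 36.5.

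**5. Safety.** The documents give no expected rate for the composite safety endpoint, so every input is assumed. Take 10/100 events in each arm as randomised, and s = 5. If 3 of the 5 switchers have an event, the literal rule gives 7/95 = 7.4% against 13/105 = 12.4%, an apparent 5-point advantage for flecainide where there is none. If switchers have the same 10% risk as everyone else (0.5 expected events), it gives 9.5/95 = 10% against 10.5/105 = 10%, and nothing moves.

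**The case against.** The strongest reply is that this is a slip for treatment assigned. The sentence names intention to treat, sets compliance and changes aside, is followed by a contrasting per-protocol analysis, and the principle is restated at the end of the section. That reading is plausible. It means a reader should not conclude that the plan is plainly as-treated and breaks randomisation for every endpoint; the text supports self-contradiction, not that. The reply does not remove the defect, because the only stated definition remains wrong and no other sentence corrects it. Nor is this detail left to a statistical analysis plan: the article states the rule, and states it wrongly.

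A reader might also infer that the rule fails because flecainide patients who do not convert have been given both drugs, some 35 of 100 on the planned rate (100 − 65). This does not show misclassification. The sentence disregards treatment changes, so on its most natural reading these patients stay in the flecainide arm, and the switch falls after the primary window in any case. The 65% is also a 4 h rate, not the 6 h rate.

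Finally, one might say that the bias must favour flecainide. That needs initial crossover, and crossover by patients with a poor prognosis. Drug choice is by randomisation at a visit that coincides with screening (Section 3.5.2), which leaves little time for departures, and the documents do not signal that any are expected. Scenario C shows that the direction can reverse.

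**Conclusion.** Wrong as written. The definition of intention to treat in Section 3.8 contradicts the principle and its own second half, and no other statement supplies the rule of analysis by randomised arm. That conclusion rests on the text alone and is firm.

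The consequence is conditional. It arises only where initial treatment differs from allocation or is never given. Over the assumed range of 0 to 10 switchers per 100, the two analyses differ by between 0 and about 11 points on cardioversion, in either direction. Against a planned difference of 42 points this would be unlikely to overturn the efficacy conclusion. A shift on the safety comparison could matter more, but the documents give no rates from which to size it.

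**What to change.** Replace the explanatory clause in Section 3.8 with: *All randomised patients are analysed in the arm to which they were randomly assigned, regardless of treatment received, compliance or later treatment.* Let the closing statement of intention to treat in that section refer to this definition. If an analysis by treatment received is wanted, for instance for safety, label it as a sensitivity analysis. Carry the same sentence into the statistical analysis plan.

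The cost is one sentence. Sample size, data collection and patient care are unchanged. It should be done before outcome data by arm are seen, so that the choice between the two readings is not made after the fact.

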## 2. Objectives

The primary goals of this clinical trial are to prove the superiority of flecainide over amiodarone in the successful cardioversion of paroxysmal atrial fibrillation at the Emergency Department and to prove that the safety of flecainide is non-inferior to amiodarone in patients with coronary artery disease without residual ischemia and an ejection fraction over 35%. The secondary goals of the study are to prove the superiority of flecainide over amiodarone in the reduction in hospitalizations from the Emergency Department due to atrial fibrillation in the time taken to achieve cardioversion, and in the reduction in the need to conduct electrical cardioversion. A successful cardioversion is defined as the restoration of the sinus rhythm, documented by a 12 lead ECG lasting at least 1 h. 

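### The safety non-inferiority goal is decided by an intention-to-treat analysis that is defined as treatment given, with no requirement that a second analysis set agree

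*Protocol article*

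**What the plan says.** Section 2 (Objectives) sets two primary goals. One is superiority on cardioversion. The other is "to prove that the safety of flecainide is non-inferior to amiodarone in patients with coronary artery disease without residual ischemia", with an ejection fraction over 35%. Section 3.7 gives the safety endpoint as "the combined frequency of PVCs, NSVT, SVT, bradycardia and hypotension during the same time frame", and Table 3 runs that window for 6 h from drug initiation.

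Section 3.8 sets one analysis rule for both goals: "All primary and secondary endpoints will be analyzed according to the “intention to treat” principle". The same sentence explains the principle as "according to the treatment given, without reference to the treatment compliance or changes". The next sentence reads "Additional per-protocol sensitivity analyses will be performed". The section's last sentence repeats the intention-to-treat label. Nothing gives the non-inferiority goal a rule of its own or asks that the two analyses agree.

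Section 3.5.2 says that with hemodynamic instability, or a 1 h troponin change above the laboratory limit, "the administration of the drug will cease, and the patient will be treated according to the guidelines". Section 3.6 gives flecainide "throughout the 10 min in the emergency department" and amiodarone "over 1 h in the emergency department, as well as a follow-up dose" that may run for up to 24 h.

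**The concern.** There are two problems with the stated rule.

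First, intention to treat means analysis by randomised arm, whereas treatment given is an as-treated definition. The article uses both for the same analysis. Under the as-treated reading, a patient given the other drug changes arm and a patient given no drug belongs to neither, so the protection of randomisation is lost in an open-label trial.

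Second, under the randomised reading, the rule is cautious for superiority but not for non-inferiority. An undosed patient has a background event risk in either arm, which pulls the two rates together. Non-exposure is possible: allocation is open (section 3.3), inclusion is dated from consent (section 3.5.1), and recent-onset fibrillation can convert before the infusion starts.

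The planned per-protocol analysis is not an assured safeguard. Systolic pressure below 90 mmHg is part of the safety endpoint, and instability is a reason to stop drug. A set that excluded stopped patients would exclude their events too. Exclusion criterion 5b in Table 1 adds to this. It turns on the 1 h troponin change, but Table 2 places that sample at the intervention visit and section 4 places it after the intervention has started. A patient could therefore fail an eligibility criterion on a value measured after dosing.

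At stake is a safety conclusion for a drug that section 4 describes as contraindicated in patients of this kind.

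**Working it through.** **The plan's own figures.** Section 3.4 gives 96 per arm. This reproduces from a two-sided 5% comparison of 65% with 45% at 80% power:

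(1.96 × √(2 × 0.55 × 0.45) + 0.8416 × √(0.65 × 0.35 + 0.45 × 0.55))² / 0.20² = (1.379 + 0.580)² / 0.04 = 95.9, so 96.

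Those are cardioversion rates, so the figure does not bear on safety. The article gives no safety event rate, safety margin or undosed share. Everything below is therefore an illustration on assumed inputs.

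**Dilution in the randomised set.** Assumed: 100 per arm, true rates 25% (flecainide) and 15% (amiodarone), margin 10 points, background rate b = 5% in undosed patients, and the same undosed share f in each arm.

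- Observed rate = (1 − f) × p + f × b
- SE = √(p₁(1 − p₁)/100 + p₂(1 − p₂)/100), using the observed rates
- One-sided error = Φ((0.10 − difference)/SE − 1.96)

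| f | Observed rates | Difference | SE | One-sided error |
|---|---|---|---|---|
| 0% | 25.0% vs 15.0% | 10.0 points | – | 2.5% |
| 2% | 24.6% vs 14.8% | 9.8 points | 0.0558 | 2.7% |
| 5% | 24.0% vs 14.5% | 9.5 points | 0.0554 | 3.1% |
| 10% | 23.0% vs 14.0% | 9.0 points | 0.0545 | 3.8% |

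**Second model.** Here only the flecainide arm has undosed patients, and they carry the comparator rate. With comparator rates of 7% to 50% and margins of 10 to 20 points, the error is 2.7% to 3.0% at f = 2%, 3.0% to 3.9% at f = 5%, and 3.5% to 5.9% at f = 10%. For scale, section 3.4 expects no substantial dropout and recruits 200 against 192 needed, an allowance of 8/200 = 4%.

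**A per-protocol set that drops stopped patients.** If a share s of the patients with events is removed, the rate becomes p(1 − s)/(1 − ps).

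- s = 30% in both arms: 0.175/0.925 = 18.9% vs 0.105/0.955 = 11.0%. The difference is 7.9 points.
- s = 50% in both arms: 0.125/0.875 = 14.3% vs 0.075/0.925 = 8.1%. The difference is 6.2 points.
- s = 5% for flecainide and 40% for amiodarone: 0.2375/0.9875 = 24.1% vs 0.09/0.94 = 9.6%. The difference is 14.5 points.

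The true difference is 10 points in each case. The last case follows the infusion times: a 10-minute infusion is over before a 1 h troponin result or later instability can stop it, whereas amiodarone is still running. The set can therefore narrow or widen the difference, depending on shares that the article does not give.

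**The case against.** The strongest reply is that section 3.8, read literally, analyses by treatment given. An undosed patient then sits in neither arm and no dilution arises. The endpoint window also starts at drug initiation, so an undosed patient has no window, and the article does not say that such patients count as background observations. Both points stand as far as they go. However, the label is used twice, and the words about compliance and changes fit a randomised set better. The result is a contradiction to resolve, not a settled as-treated plan.

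It is also fair that exposure should be nearly complete: staff give the infusion at a visit that coincides with screening, and the switch from flecainide to amiodarone comes only at 6 h. That is why the effect is small.

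A reader might infer that the safety claim rests on intention to treat alone. It does not: per-protocol analyses are planned and would be reported. What is missing is a requirement that they agree.

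A reader might also infer that both analysis sets err towards non-inferiority. The documents do not support this. The per-protocol set is not defined in the article and may properly be defined in a fuller document. Stopping drug under section 3.5.2 follows the protocol, so it need not count as a deviation. If stopped patients were dropped, the unequal infusion times leave the direction open.

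**Conclusion.** The point holds in limited form. The firm defect is the contradiction between the intention-to-treat label and its definition, which leaves the deciding set for a primary non-inferiority goal uncertain. Under the randomised reading, the rule is mildly anti-conservative: about 2.7% to 3.1% one-sided error at 2% to 5% undosed, against 2.5%, on the assumed rates, margin and background risk. It becomes more noticeable near 10% undosed, which nothing in the article suggests. The per-protocol limb is conditional. If stopped patients were removed, that analysis would be unreliable in either direction, but the article does not say that they would be. The documents do not show that the trial is likely to declare non-inferiority wrongly for these reasons. The case for change is that it is cheap and makes clear which patients decide the safety claim.

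**What to change.** In section 3.8:

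1. Replace the definition by treatment given with analysis according to the randomised arm, and keep the rest of that sentence.
2. For the primary safety endpoint only, require non-inferiority both in all randomised patients and in all patients who started the assigned drug, each analysed by randomised arm. State from what time the 6 h window runs for a patient who receives no drug.
3. State that stopping the drug for instability or a 1 h troponin change does not remove a patient from either safety analysis.
4. Keep intention to treat as the deciding analysis for cardioversion superiority.

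The cost is a few sentences and one more run on data already collected. The downside is a slightly stricter non-inferiority criterion, because both sets must agree. No dose or clinical rule changes.

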### 3.4. Sample Size

In our meta-analysis, we estimated the pooled cardioversion rate by flecainide within 4 h 65% whereas by amiodarone 23% (17). Taking 65% as our point estimate, the steering committee of FLECA-ED considers that flecainide can be regarded as non-inferior to amiodarone in patients with ischemic cardiomyopathy if the lower margin of the confidence interval does not go lower than the pooled rate (65%) by more than 20% (i.e., if it is not lower than 45%). Based on these assumptions, we expect that a sample size of 96 patients per arm is required to achieve 80% power to demonstrate the efficacy of flecainide in these patients, when a type I error rate is set at 0.05. Given the close follow-up of our patients in our registry, we do not expect a substantial dropout rate and thus aim to recruit a total of 200 (100 per arm) patients.

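### If the optional interim analysis is held, testing at 0.03 at both looks no longer gives the 80% power that was sized for one test at 0.05, and it keeps overall alpha at 0.05 only from about 55% information onwards

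*Protocol article*

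**What the plan says.** Section 3.8 makes the interim conditional: "In case of an interim analysis, the Pocock method will be used". It then fixes the levels, a p-value of "0.03 for the interim and 0.03 for the final analysis will be used". It does not say when the look would occur, which of the two primary endpoints it would test, or what follows if the threshold is crossed.

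Section 3.4 sizes the trial without mentioning an interim: "a sample size of 96 patients per arm is required to achieve 80% power", "when a type I error rate is set at 0.05". Two sets of rates appear there. The first is a pair of pooled 4 h cardioversion rates, 65% for flecainide and 23% for amiodarone. The second is a floor of 45%, which is 65% less a 20-point margin. The recruitment goal is rounded up: "aim to recruit a total of 200 (100 per arm) patients", because "we do not expect a substantial dropout rate".

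Sections 2 and 3.7 give two primary aims: superiority on cardioversion within 6 h, and non-inferiority on a combined safety endpoint over the same 6 h.

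**The concern.** Section 3.4 promises 80% power for a test at 0.05, while Section 3.8 lowers the final test to 0.03 once a look has been taken. If the interim is held, the stated power and the stated threshold cannot both stand. A constant pair of Pocock levels is also exact for only one timing of the look, and here the levels are fixed while the timing is open.

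A second matter concerns the safety aim. A group-sequential boundary is normally there to permit early stopping. If it were applied to cardioversion and crossing ended recruitment, the co-primary safety comparison would be left with whatever data had accrued by then.

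**Working it through.** **Inputs.** From Section 3.4: rates 65%, 45% and 23%; alpha 0.05; power 80%; 96 and 100 per arm. From Section 3.8: 0.03 at each look. Assumed: two-sided tests (sidedness is not stated), and one look at half information unless another fraction t is given.

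**1. The plan's sample size.** For two proportions with pooled variance under the null:

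n = [1.960·√(2·0.55·0.45) + 0.8416·√(0.65·0.35 + 0.45·0.55)]² / 0.20² = [1.960·0.7036 + 0.8416·0.6892]² / 0.04 = 95.9, so 96 per arm.

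This matches the stated figure. Alternatives do not: one-sided 0.05 gives 76, a continuity correction gives 106, non-inferiority at 65% in both arms with a 20-point margin gives 90 (one-sided 0.025) or 71 (one-sided 0.05), and 65% vs 23% gives 21. The single-test power is 80.0% at 96 and 81.6% at 100 per arm.

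**2. Power under 0.03/0.03, 65% vs 45%.** The critical value is z = 2.170 at each look. The two statistics are treated as bivariate normal with correlation √t. At 96 per arm the standard error of the difference is 0.0703 under the alternative and 0.0718 under the null. The final mean is therefore 0.20/0.0703 = 2.843, the interim mean is 2.843·√0.5 = 2.010, and the rescaled critical value is 2.170·0.0718/0.0703 = 2.215.

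| Per arm | One test at 0.05 | Final test alone at 0.03 | Either look at 0.03, t = 0.5 |
|---|---|---|---|
| 96 | 80.0% | 73.5% | 75.7% |
| 100 | 81.6% | 75.4% | 77.5% |

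The shortfall hardly depends on timing. For t from 0.25 to 0.9, the same calculation gives 75.1% to 76.1% at 96 per arm and 76.8% to 77.8% at 100.

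**3. Overall alpha under 0.03/0.03.** This is 1 − P(|Z₁| < 2.170 and |Z₂| < 2.170), with correlation √t.

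| t | 0.25 | 0.33 | 0.50 | 0.55 | 0.67 | 0.75 |
|---|---|---|---|---|---|---|
| Overall alpha | 0.0555 | 0.0541 | 0.0510 | 0.0500 | 0.0472 | 0.0450 |

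The exact two-look Pocock level at t = 0.5 is z = 2.178, or p = 0.0294. The plan's 0.03 is that value rounded up.

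**4. Chance of crossing p < 0.03 at 50 per arm.** The normal approximation is Φ[(d − 2.170·SE₀)/SE₁], where d is the rate difference and SE₀ and SE₁ are its standard errors under the null and the alternative.

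- 65% vs 23%: (0.42 − 2.170·0.0993)/0.0900 = 2.27, or 98.9% (exact enumeration: 98.9% chi-square, 98.1% Fisher).
- 65% vs 45%: (0.20 − 2.170·0.0995)/0.0975 = −0.16, or 43.5% (exact: 46% chi-square, 38% Fisher).

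**5. Safety precision.** The article states no composite rate or margin. At any common rate p, the 95% half-width for the difference is 1.96·√(2p(1−p)/n), so going from 100 to 50 per arm multiplies it by √2 = 1.41. For assumed rates from 10% to 50%, it goes from 8.3–13.9 points to 11.8–19.6 points.

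**6. Alternative levels at t = 0.5, 65% vs 45%.** Pocock 0.0294/0.0294 spends 0.0500 and has 75.4% power at 96 and 77.2% at 100 per arm; about 107 per arm restores 80%. O'Brien-Fleming 0.0052/0.0480 (constant 1.977) spends 0.0500 and has 79.7% and 81.3%.

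**The case against.** Pocock is a legitimate prespecified boundary, the look is optional, and the article condenses a longer document. Timing, trigger and stopping consequences may be set out in a full protocol, analysis plan or charter that is not shown. Their absence is not the fault raised here, nor is the question of who would decide to look. If another document fixes the look at 55% information or later, the alpha point falls away. Even at half information the excess is 0.001, a rounding effect. All of that stands. It does not remove the power point, because Sections 3.4 and 3.8 disagree as printed whenever the look occurs.

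A reader might also infer more than the article supports:

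- **That the rule both costs power and would almost surely stop the trial.** These belong to different scenarios. The power loss arises under 65% vs 45%, where a half-way look crosses about 44% of the time. Near-certain crossing arises under 65% vs 23%, where full-sample power at 0.03 exceeds 99.9% and nothing material is lost. Those rates are also for 4 h, while the endpoint is at 6 h.
- **That the boundary is for efficacy only and that crossing ends recruitment.** Section 3.8 says neither.
- **That early stopping would leave safety unanswerable.** With no margin or expected rate in the article, this cannot be judged even at 100 per arm. Only the loss of precision can be stated.

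**Conclusion.** The point holds as an inconsistency between the sample size and the interim rule. If the look is held, power is about 4 points below the stated 80% at 96 per arm. Rounding up to 100 per arm does not repair this: 77.5%, against 81.6% for a single test at 0.05. This rests on two-sided testing and on 65% vs 45%, the pair that reproduces 96.

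The alpha point is secondary. Fixed levels of 0.03/0.03 overspend by 0.001 at half information and by about 0.005 at one quarter, and do not overspend from about 55%.

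The safety point is conditional. Only if crossing led to stopping at half the sample would the co-primary safety comparison have half its information and an interval about 1.4 times as wide. The article should rule that out or say that it is accepted.

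**What to change.** Choose one of the following in Section 3.8 and make Section 3.4 agree with it.

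1. **No efficacy look.** Any interim review is for harm only, and the final efficacy test is at two-sided 0.05. The sample size then stands. The cost is wording, and no early efficacy stop is possible.
2. **Keep Pocock.** Fix the look at 100 patients, use 0.0294/0.0294, and restate power as about 77% at 100 per arm. Alternatively, recruit about 107 per arm (214 in total) for 80%, which costs 14 more patients than planned.
3. **Use O'Brien-Fleming levels.** With the look at 100 patients, 0.0052/0.0480 gives about 80% power at 96 and 81% at 100 per arm. The cost is a lower chance of crossing early. If the timing must stay flexible, use an alpha-spending function in place of fixed levels.

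Under options 2 and 3, name the endpoint tested at the interim, and state that an efficacy crossing does not end recruitment before the co-primary safety comparison is complete. Making an early stop depend on meeting safety non-inferiority would not work as the article stands, because it gives no margin.
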